### Blinding

In this study residents, therapists and interviewers collecting data for the qualitative part of the study were not blinded. Therapists are encouraged to present both the experimental and the control condition with equal enthusiasm.

### Experimental condition

Subjects in the experimental condition are assigned to the life review-based prevention course 'Looking for Meaning' for people aged 55 and older [17]. Groups are typically consisting of eight participants. They are conducted by two mental health care professionals with a therapeutic background or an education in behavioral sciences (e.g., psychology) or social work, who for this purpose receive a two-day training program in advance and one day during the course. The 12 sessions of two hours each are similarly structured, including sensory recall exercises, creative activity, and verbal exchange of experiences. Each session is centered on a topic related to the course of life, also making an explicit link between the past and the present.

Meetings are entitled: your name; smells from the past; houses you've lived in; recognizing your resources; hands; photographs; friendship; balance; thread of life and turning points; longing and desire; the future in me; and identity. Participants are encouraged to make use of the senses in order to evoke memories. In addition, creative exercises may open up new ways of expression besides the verbal mode. The course also offers the possibility of further reading and reflection; poems, short stories and literature suggestions are included in the course material.

Based on the experiences of participants in the pilot study [18], three sessions have been replaced or changed. Participants in the pilot indicated that they missed verbal exchange, and would also like to learn about problem solving techniques. These elements were included in the course after the pilot.

### Control condition

The participants assigned to the control group receive an invitation to come watch 'The Art of Growing Older' [23]. This 20-minute educational video movie supplies information about factors and skills that promote growing older successfully. This intervention is considered a minimal intervention, as no treatment is involved.

### Quantitative study

#### Data collection

##### Overview

Table 1 provides an overview of the economic and effect measurements. As a part of the intake and selection interview, we administer the Center for Epidemiological Studies Depression Scale (CES-D), in order to screen the participants. The outcome is considered the CES-D baseline score for those included; the course starts shortly thereafter. Data at t0 (baseline), t1 (effect; 3 months after t0), and t2 (retention; 6 months after t1) are collected by means of a questionnaire. Demographics and additional personal characteristics are recorded at t0 only, and evaluation questions about the participant's experience with the intervention are asked only at t1. Except for that, the three questionnaires are identical.

**Table 1 T1:** Measurement overview per time (intake, t0, t1, and t2) and research section (clinical, economic and qualitative study)

Variables per research section	Instrument	Intake	T0	T1	T2
Screening and selection					
Examine for depression if CES-D ≥ 16	MINI	×			
Clinical effect evaluation					

*Primary outcome*					
Depressive symptoms	CES-D	×		×	×
					
*Secondary outcomes*					
Anxiety	HADS-D		×	×	×
Locus of control; mastery	Pearlin Mastery Scale (5 items)		×	×	×
Satisfaction with life	MANSA (12 items)		×	×	×
					
*Reminiscence functions*	RFS (4/8 subscales)				
Boredom reduction			×	×	×
Bitterness revival			×	×	×
Identity			×	×	×
Problem solving			×	×	×
					
Economic evaluation					

Cost associated with the receipt of care	TIC-P		×	×	×
Quality of life	EQ 5-D		×	×	×
					
Qualitative study					

Interviews with participants			×			
Observation			×			

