### Participants

Participants are recruited via advertisements in local and national newspapers, magazines targeted at an older audience, or selected with the help of professionals affiliated to one of eleven regional institutes for mental health care in both rural and urban areas of the Netherlands participating in this study. These mental health care institutes support the participant recruitment and -intake, make available the professionals needed, and eventually take care of organizing and offering the course within their institute.

In order to participate in this study, participants have to show slight to moderate depressive symptoms; people diagnosed with a major depression are excluded, as well as people showing no symptoms at all. The intended population is aged 55 and up, as the course was developed for older adults. People who respond, are screened for depressive symptoms by mental healthcare professionals (e.g., a psychologist or a therapist). People scoring 24 or higher on the Center for Epidemiological Studies Depression Scale (CES-D), are further examined with the Mini International Neuropsychiatric Interview (MINI) in order to decide whether a major depression is present or not [19-21]. People with scores below 5 are excluded from the study as well, because improvement is hardly possible. People eligible to participate are asked to complete the consent form.

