### Analyses

The analyses will be performed according to the íntention to treat' principle. Therefore, all missing values were imputed. In order to replace the missing values by plausible estimates, we will use the regression imputation procedure as implemented in Stata version 9.1 [31].

We will calculate effect sizes for the immediate improvement of the experimental and the control group on the primary and secondary outcomes by dividing the absolute difference between the post-treatment average score and the pretreatment average score by the pretreatment standard deviation. To establish the maintenance of improvement of both groups, effects sizes will be calculated by dividing the absolute difference between the follow-up average score and the post-treatment average score by the pretreatment standard deviation. For between-group effect sizes, the effect size of the experimental group will be subtracted from the effect size of the control group. Effect sizes of 0.56–1.2 can be assumed to be large, while effect sizes of 0.33–0.55 are moderate, and effect sizes of 0–0.32 are small [32].

In the cost-effectiveness analyses, we will calculate the pre-post changes in costs and identify which respondents show a moderate to large improvement in depressive symptoms in both conditions. These respondents changed reliably, and could thus be considered a 'success'. Then we calculated the incremental cost-effectiveness ratio (ICER) across the experimental and control condition, which represents the incremental costs (or savings) per 'success' (i.e. moderate to large improvement in depressive symptoms) in the experimental condition relative to the control condition. Uncertainty will be assessed by means of non-parametric bootstrapping (2,500 times) of the data of the individual respondents.

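### The CES-D score used to select participants is also the only pre-treatment value of the primary outcome, so within-arm effect sizes absorb regression to the mean and every CES-D effect size is scaled by a selection-restricted SD

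*Protocol article*

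**What the plan says.** All references are to the protocol article.

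- **Overview (Data collection).** The CES-D is first given at intake, for screening: "As a part of the intake and selection interview, we administer the Center for Epidemiological Studies Depression Scale (CES-D), in order to screen the participants". That score then becomes the baseline: "The outcome is considered the CES-D baseline score for those included; the course starts shortly thereafter".
- **Overview, questionnaires.** "Data at t0 (baseline), t1 (effect; 3 months after t0), and t2 (retention; 6 months after t1) are collected by means of a questionnaire". Apart from demographics (t0 only) and evaluation questions (t1 only), the text adds: "Except for that, the three questionnaires are identical".
- **Table 1.** The row "Depressive symptoms CES-D" is ticked at intake, T1 and T2 and is blank at T0. Every other clinical and economic outcome (anxiety, mastery, life satisfaction, the four reminiscence subscales, costs, EQ-5D) is ticked at T0, T1 and T2.
- **Participants.** Selection uses this same score. At the bottom: "People with scores below 5 are excluded from the study as well, because improvement is hardly possible". At the top, a score of 24 or higher leads to the MINI, and people found to have major depression are excluded. Table 1 gives the MINI trigger as 16 or higher. Consent comes next: "People eligible to participate are asked to complete the consent form".
- **Analyses.** The immediate effect size in each arm is obtained by "dividing the absolute difference between the post-treatment average score and the pretreatment average score by the pretreatment standard deviation". The maintenance effect size takes follow-up minus post-treatment over the same SD. The between-group effect size is the difference of the two arms' values. Values of 0-0.32 are called small, 0.33-0.55 moderate and 0.56-1.2 large. For the cost-effectiveness ratio, a respondent with moderate to large improvement in depressive symptoms counts as a success.

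**The concern.** A score that decides who enters a trial is a poor yardstick for change in those who entered. Cutting off low scores leaves a group whose intake mean is somewhat too high, so the next measurement tends to fall without any treatment. Removing some high scorers pulls the other way. Either way, the spread of the selected score is usually narrower than that of a fresh measurement in the same people.

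The Analyses section uses this score twice for the primary outcome: as the starting mean of the immediate change, and as the SD that divides both the immediate and the maintenance change. The first use puts a drift unrelated to the course into each arm's pre-post effect size. It also affects individual success, if success is measured from baseline, which the article does not state. The second use enlarges all CES-D effect sizes just before they are graded against fixed cutoffs. The primary outcome is the only clinical or economic outcome treated this way.

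The documents also disagree with themselves. If the three questionnaires are identical, the CES-D is in the t0 questionnaire and Table 1 is wrong. If Table 1 is right, the statement about the questionnaires is wrong.

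**Working it through.** **What there is to reproduce.** The article gives no CES-D mean, SD or retest correlation, so no figure of its own can be reproduced and the size must rest on stated assumptions.

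**Step 1: which quantities are touched.** Let X be the intake score of those enrolled, D the drift of the mean caused by selection alone, and τ the effect of the course at t1 in CES-D points.

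- Within-arm immediate effect size: |mean(t1) − mean(X)| / SD(X). Contains D, and is divided by SD(X).
- Maintenance effect size: |mean(t2) − mean(t1)| / SD(X). The numerator is free of X; only the divisor is affected.
- Raw between-arm contrast: both arms are selected by one rule before randomisation, so mean(X) and D are equal in expectation and cancel, leaving τ.
- Standardised between-arm contrast at t1: τ / SD(X). Against the SD of an unselected re-measurement Y of the same people, it is too large by the factor SD(Y) / SD(X).

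**Step 2: a worked case (assumed values).** Applicants normal with mean 18, SD 9, retest correlation 0.75; scores below 5 excluded; a share of those at or above the MINI trigger excluded.

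| MINI trigger | share excluded | SD(X) | SD(Y) | SD(Y)/SD(X) | drift Y − X, points |
|---|---|---|---|---|---|
| 24 | 0% | 7.82 | 8.36 | 1.069 | −0.35 |
| 24 | 50% | 7.05 | 7.95 | 1.128 | +0.06 |
| 24 | 100% | 5.02 | 7.06 | 1.405 | +0.59 |
| 16 | 50% | 7.74 | 8.31 | 1.074 | +0.20 |

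The drift changes sign with the share excluded, so its direction cannot be known in advance. The 100% row is a hard upper cut, which the protocol does not set: it excludes on diagnosis, not on score.

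**Step 3: a range of assumptions.** Mean 14-22, SD 8-10, retest correlation 0.6-0.8, scores below 5 excluded, 0-50% of those at 24 or more excluded.

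- Normal scores: SD(Y)/SD(X) runs from 1.02 to 1.31, median about 1.10; about 8% of settings exceed 1.20. Drift with no treatment runs from about 0.17 SD of apparent improvement to about 0.09 SD of apparent worsening.
- Non-negative, right-skewed (gamma) scores with the same means and SDs: about 1.00 to 1.18, median about 1.04.

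The maximum of 1.31 occurs at mean 14, SD 10, correlation 0.6 and 50% exclusion. There the normal model puts Φ((0 − 14)/10) = Φ(−1.4) ≈ 8% of applicants below zero on a 0-60 scale, so that corner fits badly.

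**Step 4: what this does to the grading.**

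- To lift a true 0.30 to the moderate boundary takes 0.33 / 0.30 = 1.10, the median under the normal model.
- At the skewed-model median, only values from 0.33 / 1.04 ≈ 0.32 upward are lifted across.
- In the extreme corner, 0.30 × 1.31 = 0.39.
- If individual success used 0.33 SD from baseline (an assumption), the threshold in the 24/50% row would be 0.33 × 7.05 = 2.3 points instead of 0.33 × 7.95 = 2.6.

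**The case against.** The best defence is that this is a disclosed choice. The text and Table 1 agree that the intake score is the baseline, the course is said to start soon afterwards, and reusing the score spares participants the same 20 items twice in a short time. The intake score necessarily precedes allocation. The article does not say whether the t0 questionnaire does, and neither the therapists nor the group it calls residents are blinded, so a t0 CES-D is cleaner only if it is completed before allocation is known. Standardising by the enrolled sample's own baseline SD is common practice. All of this stands, and it limits the point to the interpretation of effect sizes.

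Several stronger readings are tempting but not supported:

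- **That the comparison between arms is biased.** It is not. Selection precedes randomisation and is the same for both arms. What remains is a scale factor that cannot produce an effect, reverse its sign or favour one arm.
- **That every CES-D change starts from the intake score.** The t2-minus-t1 change does not; only its divisor does.
- **That the intake score is noisier or was collected in another mode.** The article describes the CES-D as self-report. Only the setting differs, and nothing is said about reliability.
- **That the score is materially out of date.** It is earlier than t0 by an unstated gap that the text suggests is short.
- **That inflation of about 30% is to be expected.** It arises in one corner of one assumed model.

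Adding the CES-D at t0 may also come too late: the Sample size section reports inclusion at t0 in the past tense. The fallback below does not depend on it.

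**Conclusion.** The point holds for effect sizes, not for the randomised contrast. The selection score is the only pre-treatment CES-D on record in Table 1. The within-arm immediate effect sizes on the primary outcome therefore mix the course effect with regression to the mean of unknown direction, and all CES-D effect sizes share a divisor narrowed by selection.

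The size is probably modest: roughly 0-30% inflation over the assumed range, with a median near 4% for skewed scores and near 10% for normal ones. That is enough to regrade a value lying close to 0.33, and no more. These figures depend on assumed applicant means, SDs, retest correlations and score shape, and on the share of high scorers removed by the MINI, none of which the article gives. The MINI trigger is itself stated in two ways.

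Separately from any simulation, the statement that the questionnaires are identical and the blank T0 cell for CES-D cannot both be correct.

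**What to change.** **If t0 data are still to be collected.** Add the 20-item CES-D to the t0 questionnaire, completed after consent and before the participant knows the allocation. Use that score as the CES-D baseline and its SD as the standardiser. Keep the intake score for eligibility only, so that a different score at t0 does not change who is in the trial. Cost: 20 more items in a questionnaire already given, and one changed row in Table 1.

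**If t0 is past.** Make the primary between-arm comparison the raw CES-D difference at t1 and at t2, adjusted for the intake score. Adjusting for a pre-randomisation score is valid even though it was selected on, it gains precision, and the result in points does not depend on the restricted SD. State that within-arm pre-post effect sizes are not to be read as effects of the course. If standardised values are still reported, name the SD used and note that it was restricted by selection. Cost: no new data, only a change in analysis and reporting.

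**In either case.** State whether individual success is measured from baseline and in which units. Reconcile the statement on identical questionnaires with the blank T0 cell in Table 1. Reconcile the MINI trigger of 24 in Participants with the 16 in Table 1; it determines which high scorers are examined, and so how the baseline was selected.

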##### Primary outcome

1. Reduction of depressive symptoms measured using the Center for Epidemiological Studies Depression Scale (CES-D).

The Center for Epidemiologic Studies Depression scale (CES-D) is a 20-item self-report scale developed to measure depressive symptoms in the community [19]. Subjects were asked to indicate how often they experienced each symptom during the previous week. Response categories, ranging form 0 to 3, were 'rarely or never', 'some of the time', 'occasionally', or 'mostly or always'. Summation results in the CES-D score, ranging from 0 to 60. A score of 16 or higher is considered indicative for clinically relevant depressive syndromes. The psychometric properties of the scale are found to be good in older populations [20].

##### Secondary outcome

2. Reduction of anxiety symptoms measured using the Hospital Anxiety and Depression Scale (HADS)

The HADS is a 14-item, self-reporting screening scale comprising two 7-item Likert scales, measuring depression and anxiety, respectively. We use the anxiety scale (HADS-A) [24]. Respondents are asked to indicate whether they experienced feelings of restlessness, tenseness, or panic during the past four weeks. Items range from 0 (rarely or never) to 3 (always or most of the time). The total score ranges from 0 to 21.

3. An increase of satisfaction with life measured using the Manchester Short Assessment of Quality of Life (MANSA).

The Manchester Short Assessment of Quality of Life (MANSA) comprises 16 items: 4 objective questions and 12 subjective questions [25]. We use the 12 subjective items, assessing satisfaction with life as a whole, employment or retirement, financial situation, friendships, leisure, accommodation, personal safety, people that the individual lives with (or living alone), sex life, relationship with family, physical health, and mental health. Each item is rated on a seven-point scale ranging from 1 (couldn't be worse) to 7 (couldn't be better). Summary scores range from 12 to 84; the higher the score the better the quality of life.

4. An increase in perceived control over one's life, measured using the Pearlin and Schooler's Mastery Scale.

The Pearlin and Schooler's Mastery Scale consists of seven items that are intended to assess beliefs of perceived control over one's life in general or beliefs regarding one's ability to control an event [26]. We use the abbreviated version of five items, phrased in a negative way. Possible responses are given on a 5-point scale ranging from 1 (strongly disagree) to 5 (strongly agree). Summary scores range from 5 to 25. Higher scores on the scale indicate lower levels of perceived control.

5. Change or transformation into more positive reminiscence styles measured using the Reminiscence Function Scale (RFS).

The Reminiscence Function Scale is a 43-item questionnaire that can be used to assess reminiscence functions over the life course [27]. The scale comprises eight subscales (factors) reflecting possible functions of reminiscence for the individual. The subscales are labeled 'boredom reduction', 'death preparation', 'identity', 'problem-solving', 'conversation', 'intimacy maintenance', 'bitterness revival', and 'teach/inform'. Questions typically start with "when I reminiscence, it is..." and are completed with 43 possible reasons or motivations to reminiscence. Respondents are asked to indicate the extent to which each of the 43 reasons apply to them. Possible answers range from 1 to 6 (never, rarely, seldom, occasionally, often, or very frequently). For the purpose of this research, 23 questions covering four subscales have been selected: 6 about boredom reduction, 6 about identity, 6 about problem-solving, and 5 about bitterness revival. Examples are: "When I reminisce, it is... to pass the time during idle or restless hours" (boredom reduction), "to see how my past fits in with my journey through life" (identity), "to help me plan for the future" (problem solving), or "to keep painful memories alive" (bitterness revival). Scores are averaged per subscale, representing a reminiscence function each. The higher the score, the more the indicated function applies. In addition, the summary score (all items) indicates the extent to which a person reminiscences irrespective of its reason or function.

##### Additional measures: confounding or modifying variables

In addition to the measurements mentioned above, we assess the following variables that may act as modifying factors of primary and secondary outcomes: Chronic disorders (such as coronary diseases, lung diseases, or rheumatism) critical life events within in the past three years (such as the lost of a spouse, divorce, or having moved), socioeconomic status (SES) according to employment, finances, level of education, and living arrangement.

##### Economic evaluation

The aim of the economic evaluation is to estimate the incremental cost-utility in terms of quality-adjusted life years (Qualy) gained in the treatment group, as compared to the non-treatment group. The economic evaluation is based on the EQ-5d and the Tic-P. Costs of the intervention itself are estimated as well. Measures are described below.

9. An increase of quality of life as measured with the EQ-5D.

The EuroQoL EQ-5D is a pre-scored health classification system that is defined over five domains of health: mobility, self-care, usual activity, pain/discomfort and depression/anxiety [27-29]. Each of the five domains is categorized into three severity levels; 0 (none), 1 (some) and 2 (severe). Responses are combined by a scoring algorithm to produce a summary utility score between -0.594 and 1.0, where 1 represents the state of best imaginable health. Values correspond with Quality-adjusted life years (Qualy) gained or lost. We use an index based on the Dutch population, in accordance with the Dutch TTO tariff [29]. In our study, we also use the EQ-5D as a clinical outcome measure indicating one's perceived quality of life.

10. A decrease in costs of receiving (in)formal health care as measured with the TIC-P.

Cost data are collected using the TIC-P [30]. Costs are defined from a societal perspective and include direct and indirect costs related to receiving formal and informal health care. Production losses in both paid and unpaid work are also covered by the TIC-P. These costs arise when people are absent from work, or work less efficiently due to depression, for example. Production losses will be estimated with the help of the TIC-P.

